### Measures and Data Collection

The primary outcome of Alive-PD is change in HbA1c and fasting glucose at 6 months from baseline, assessed through point-of-care whole blood samples (see Baseline Assessment and Clinic Visit, above). Secondary endpoints are clinic-measured changes in other biometric measures (weight, waist circumference, lipids and other metabolic syndrome factors, and blood pressure). We will examine retention of changes at 12 months in a pre-post analysis. In addition, we will examine self-reported behavior changes in eating and physical activity.

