## Methods

### Study Design Overview

The Alive-PD study is a randomized parallel-group controlled trial of the Alive-PD program versus a 6-month-delayed control group among participants with pre-diabetes. The primary outcome measures are change in hemoglobin A1c (HbA1c) and fasting glucose after 6 months. After the study began, the follow-up period was extended to 12 months for both arms. We hypothesize that those in the intervention group will achieve statistically significantly greater reductions in fasting glucose and HbA1c than a delayed-entry control group at 6 months post baseline and that the intervention group will retain a statistically significant change at 1 year. Clinic assessments and laboratory data are collected at 3, 6, 9, and 12 months. The trial is ongoing.

This randomized clinical trial is being conducted in collaboration with the Palo Alto Medical Foundation Research Institute (PAMFRI). The study design and materials were approved by the Institutional Review Boards of NutritionQuest and of the Palo Alto Medical Foundation (PAMF). See Multimedia Appendix 1 for the CONSORT-EHEALTH checklist [21].

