#### Baseline Assessment and Clinic Visit

At the baseline clinic visit, HbA1c, fasting glucose, total and high-density lipoprotein (HDL) cholesterol, triglycerides, and low-density lipoprotein (LDL) by calculation were assessed through point-of-care whole blood samples (Siemens DCA Vantage point-of-care analyzer [22] and Alere Cholestech LDX point-of-care analyzer [23] respectively). In addition to meeting other eligibility criteria, subjects were deemed eligible if either HbA1c and/or fasting glucose fell within the pre-diabetic range, and neither measure reached the diabetic range. A number of subjects who were eligible by one measure were found to have quite low HbA1c or fasting glucose; a further restriction, HbA1c ≥5.3% and glucose ≥95, was added after the study had begun. Prospective participants with one measure in the diabetes range and the other in the pre-diabetes range were deemed provisionally eligible pending physician review and verification of pre-diabetes status. Signed informed consent was obtained.

Other biometric measures included blood pressure, height, weight, and waist circumference, measured according to the procedures recommended by the Airlie Conference. In addition, a baseline questionnaire was administered, assessing medication use, adverse events and participation in activities relevant to weight loss, diet, and physical activity. With separate consent, a blood sample was obtained by FTA (Flinders Technology Associates) card for future research on genetic analysis of the intervention’s efficacy and disease progression.

Once enrolled and confirmed eligible, subjects received brief (5-10 minutes) instruction that they were at risk for developing diabetes and that increased physical activity as well as changes in their dietary behaviors could help prevent progression to diabetes. Research staff assisted participants in signing into an account for the Alive-PD Web-based program, to confirm to the Alive-PD system that they had completed the informed consent and to provide their email address and password to the system. All subsequent communications from and interactions with the electronic Alive-PD program took place outside of the clinic.

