#### Randomization and Blinding

After the baseline clinic visit and the initial account set-up, randomization and delivery of the intervention is conducted electronically by the Alive-PD program, completely independent of clinic staff. After leaving the clinic, participants are sent an introductory email from the automated Alive-PD system, with further information and questionnaires. These and all further online interactions are done at a time and place of the participants’ choosing. An online baseline questionnaire is required, to provide demographic and BMI information required for randomization and to provide brief eating habits and physical activity data for baseline comparison of intervention and control groups. Participants are randomized by computer algorithm, with blocked stratified randomization to achieve balance on sex, BMI (above/below 35), and race/ethnicity (white non-Hispanic, other). Participants are informed by the system by email about whether they have been randomized to begin the program immediately or after a 6-month delay. Those in the delayed group receive no further contact until a reminder to complete a 3-month and 6-month online follow-up questionnaire. Those randomized to begin immediately receive a more extensive diet and activity questionnaire.

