### Preliminary Outcome Results

Preliminary data on treatment-control differences indicate a statistically significant treatment effect on HbA1c, fasting glucose, and body weight (data reported elsewhere). These significant treatment effects were seen despite the fact that the control group achieved a statistically significant (*P*<.01) reduction in HbA1c and weight.

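### The planned pre-post test at 12 months cannot show that the program's effect was retained: no program-free arm remains, and the control arm itself improved on HbA1c and weight

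*Protocol article*

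**What the plan says.** Study Design Overview joins a 1-year hypothesis to the 6-month one: it expects that "the intervention group will retain a statistically significant change at 1 year". Measures and Data Collection names the method: "We will examine retention of changes at 12 months in a pre-post analysis". Neither place states the arm and both time points in full. Read together, they most naturally mean the intervention arm at 12 months against its own baseline.

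The 12-month period was a later addition: "After the study began, the follow-up period was extended to 12 months for both arms". Under Randomization and Blinding, participants are "randomized to begin the program immediately or after a 6-month delay". Before their start, controls have no program contact: "Those in the delayed group receive no further contact until a reminder to complete a 3-month and 6-month online follow-up questionnaire". Under Baseline Assessment and Clinic Visit, entry depended on the HbA1c or glucose reading taken at the baseline visit, and all enrolled "subjects received brief (5-10 minutes) instruction that they were at risk for developing diabetes". Preliminary Outcome Results reports that "the control group achieved a statistically significant (*P*<.01) reduction in HbA1c and weight". It gives neither the size nor the time point of that reduction, and does not list glucose.

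**The concern.** A test against baseline attributes to the program everything that moves the mean over a year. Here at least three other causes are plausible:

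- regression to the mean, because the visit that decides entry also supplies the baseline value;
- the diabetes-risk and lifestyle instruction given to both arms;
- repeated measurement and secular change.

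Normally a concurrent control would remove these. From month 6 the controls are on the program, so at month 12 an arm contrast compares about 12 with about 6 months of exposure, not program with no program.

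There is a second, separate problem. Significance against baseline is not a test of retention. An arm can lose much of what it had gained by month 6 and still differ from baseline.

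At stake is the durability claim for a one-year program. As written, the 1-year hypothesis could be declared met when the program had no effect, or when most of its effect had gone.

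**Working it through.** **The plan's own figure.** No sample size or power is given for the 12-month analysis. The only stated calculation is for the 6-month HbA1c comparison, and it reproduces: a difference of 0.48, SD 1.4, two-sided alpha .05 and 80% power give 134 per arm, 268 in all (power 80.1%). Enrolment is 268/0.85 = 316 against 314 stated, which is close enough.

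**Inputs for the check.**
- Control arm n=176, intervention arm n=164 (Table 1).
- Control within-group P<.01 (Preliminary Outcome Results).
- 15% dropout (Sample Size): 164 × 0.85 = 139.
- Assumptions: the control result came from a paired t-test on all 176; the pre-post test is a two-sided 5% paired t-test; the SD of change is the same in both arms.

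**Step 1: the smallest control-arm shift consistent with P<.01.** In units of the SD of change, d = t(0.995; 175)/√176 = 0.196. If fewer controls contributed, the shift must have been larger: 0.203 at n=165 and 0.213 at n=150.

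**Step 2: give that shift to the intervention arm, with zero program effect.** The noncentrality is d√n: 0.1963 × √164 = 2.51, and 0.1963 × √139 = 2.31. The noncentral t-distribution gives the chance of a significant reduction. The true shift at 12 months is unknown, so it is varied:

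| Shift at 12 months as a multiple of 0.196 SD | n=164 | n=139 |
|---|---|---|
| 0 (nominal) | 0.025 | 0.025 |
| 0.25 | 0.09 | 0.08 |
| 0.5 | 0.24 | 0.21 |
| 0.75 | 0.47 | 0.41 |
| 1 | 0.71 | 0.63 |
| 1.25 | 0.88 | 0.82 |

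**Step 3: what this means in HbA1c points.** The documents give no SD of change for this population. For an assumed SD of 0.2 to 0.3, the shift is 0.196 × 0.2 = 0.04 to 0.196 × 0.3 = 0.06 points. At the planning SD of 1.4 it is 0.27. On the smaller SDs, a very small drift is enough.

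**Step 4: significance against baseline is not retention.** With an assumed SD of change of 0.3 and n=139, an observed change from baseline is significant once it exceeds about 1.96 × 0.3/√139 = 0.05 points. Any 6-month fall above 2 × 0.05 = 0.10 points could therefore be halved by month 12 and still pass.

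**The case against.** The primary comparison is randomized, is made at 6 months with baseline adjustment, and is untouched. The 12-month follow-up is an extension, and the article openly calls its analysis pre-post. It speaks of retaining a change, not of a retained program effect. The abstract also lists 12-month outcomes, and Data Analysis gives a between-arm model. All this is fair and lowers the severity. It does not remove the problem. The 1-year statement stands in the same sentence as the main hypothesis, and a between-arm model at 12 months would compare immediate with delayed start.

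A reader might infer more than the documents support:

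- *That the pre-post test will be positive whatever the program does.* The table shows otherwise: the rate runs from 8% to 88% over the shifts considered. The control result is preliminary and of unstated size, and an observed shift at P<.01 may overstate the true one.
- *That the controls have already passed the 12-month test.* No program-free result at 12 months exists. The control finding must come from some earlier time point if it precedes program access, and the article does not say which.
- *That the controls were wholly untreated.* They were without the program, but they received the baseline instruction.
- *That glucose must show a large spurious fall.* A simulation that admits everyone on a glucose reading of 100 to 125 gives false-positive rates of about 40% to 99%. But entry could be by HbA1c alone, and that model predicts a baseline glucose SD of 5.6 to 6.1 against 8.4 in Table 1. Lowering only the entry floor to 95 moves the range to 14% to 78%. The article reports no control-arm fall in glucose. No glucose figure is relied on here.

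**Conclusion.** The concern holds for the 12-month claim only. A significant change from baseline in the intervention arm cannot separate the program from non-program change, and it does not test whether the 6-month gain was kept. With no program effect, the chance of a significant reduction is about 63% to 71% if the intervention arm shares a just-significant control-arm shift, and 21% to 24% if that shift has halved, against a nominal 2.5%.

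These figures rest on the assumed drift at 12 months, equal SDs of change, n between 139 and 164, and reading the pre-post test as intervention arm, month 12 against baseline. The reasoning about comparators does not depend on them. This should be fixed, but the randomized 6-month result does not depend on it.

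**What to change.** Replace the 1-year hypothesis in Study Design Overview and the pre-post test in Measures and Data Collection as follows:

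1. Estimate the intervention arm's change from month 6 to month 12 with a 95% CI. Report it beside the randomized 6-month between-arm difference, and describe it as uncontrolled.
2. Show the delayed arm's change from baseline to month 6 as a benchmark for the intervention arm's change from baseline to month 12, labelled as non-concurrent.
3. Label any 9- and 12-month arm contrast as immediate versus delayed start.
4. State that 9- and 12-month data come only from those who re-consent to the extension (Reimbursement), which adds possible selection.
5. Make no efficacy or retained-effect claim from significance against baseline.

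The cost is wording and one additional estimate from visits already scheduled. The price is a more modest 12-month claim. The month 6 to 12 change remains uncontrolled, and the benchmark assumes that the change seen without the program does not continue after month 6. Precision is also limited: with an assumed SD of change of 0.3 and n=139, the CI half-width is 1.96 × 0.3/√139 = 0.05 HbA1c points. For that reason an estimate with its interval is proposed, not a pass-or-fail retention margin.

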### Statistical Analysis

#### Sample Size

Sample size was estimated using data from Davis et al [39], who conducted a dietary intervention in patients with diabetes. They reported standard deviations for change in HbA1c of 0.9-1.4% for one arm of the study. With an SD of 1.4 and an alpha of .05, a final sample of 268 participants would provide 80% power to detect a minimum detectable difference in change for HbA1c of 0.48. We planned to enroll 314 persons to achieve a completed sample of 268 after a 15% dropout rate.

#### Data Analysis

The primary approach for analyses of treatment effects on glycemic markers (HbA1c and glucose) and other biometric markers will be on the intention-to-treat population. Variables missing at follow-up will be imputed using a maximum likelihood approach. We will also repeat analyses on the per-protocol population, in which effects will be assessed among those providing follow-up biometric data and in relation to the participants’ degree of interaction with the program. Outcomes will be analyzed using linear regression models. Change in the outcome measures (HbA1c, glucose, or weight) will be included in regression models as the dependent variable, and treatment group will be included as the primary predictor variable (intervention vs delayed control). The baseline value of the outcome measure of interest will be included as a covariate. Normality, interaction, and potential confounding will also be investigated, and potential confounders will be included as appropriate. We will also examine the proportion of participants who achieve and retain categories of body weight loss, and the proportion who move from pre-diabetic to normal HbA1c. These binary outcomes will be modeled in logistic regression models with an approach similar to that described for linear regressions. Clinic staff obtaining the biometric measurements are blinded to treatment group and data analysis is conducted on masked data.

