An interactive activity planning tool forms the basis of physical activity goal setting. Alive-PD automatically creates a recommended activity plan based on a participant’s measured activity level, but the participant may edit the plan at any time. The default target is 150 minutes per week, but those already achieving that level may aim higher. As participants interact with each setting, their activity plan is instantly recomputed and drawn onscreen. Their saved plan guides the tailored aerobic activity goals recommended to the participant each week.

Two weekly Health Notes, developed by Certified Diabetes Educators and behavioral experts, provide health information. Topics include subjects such as the role of diet and physical activity in preventing diabetes and other chronic diseases, physical activity guidelines, dietary sources of saturated fat and sugars, portion control, and behavioral strategies including self-monitoring, mindfulness, stress reduction, and sleep. Each Health Note includes a quiz, and participants may rate the Health Note and share it on social media. Delivery of the Health Notes may be tailored to the ethnicity of the participant.

The program promotes social support through a team system, which allows participants to send messages to each other with either a pre-drafted motivational message or a personalized message of support. The system also encourages participants to elicit the support of their personal social network. Participants may invite friends and family to the program, and those who accept receive weekly emails from the system, which include the Health Notes the participant is reading that week and a function to send a message to the participant’s Alive-PD inbox.

Other features include a Daily Tracker to log weight, activity, and dietary intake, with automatic graphing over time; an automated coaching tool to help participants overcome common barriers; weekly infographics that reinforce core messages of the program; downloadable worksheets; and links to external resources.

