Program engagement strategies combine intrinsic and extrinsic motivators, with individual and optional team aspects and software gamification features. At the individual level, interaction with central components of the intervention is incentivized using a points system. Participants are awarded points for the following behaviors: setting and reporting goals; successfully accomplishing goals; reading Health Notes and taking the related quizzes; logging body weight, activity, or dietary intake; and sending support messages to other Alive-PD participants. Points can be redeemed for modest monetary rewards or may be contributed to a pooled donation to the American Diabetes Association. At the team level, teams compete for small monetary rewards based on the greatest average HbA1c reduction in each 3-month period.

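### The stated regressions and sample size make no allowance for possible within-team correlation, which can arise in the intervention arm only

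*Protocol article*

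**What the plan says.** All of this is in the Protocol article.

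- **Allocation (Randomization and Blinding).** The individual is the unit: "Participants are randomized by computer algorithm, with blocked stratified randomization to achieve balance on sex, BMI (above/below 35), and race/ethnicity".
- **Contact between participants (Features of the Alive-PD Program and Website).** "The program promotes social support through a team system, which allows participants to send messages to each other". The same section adds that "teams compete for small monetary rewards based on the greatest average HbA1c reduction in each 3-month period". It describes the engagement strategies as coming "with individual and optional team aspects and software gamification features", so team membership cannot be taken as universal.
- **Control arm (Randomization and Blinding).** "Those in the delayed group receive no further contact until a reminder to complete a 3-month and 6-month online follow-up questionnaire".
- **Analysis (Data Analysis).** "Outcomes will be analyzed using linear regression models". Change is the dependent variable, treatment group the main predictor and the baseline value a covariate. Confounders may be added. Binary outcomes get logistic models built in a similar way.
- **Sample size (Sample Size).** 268 completers, from an SD of 1.4, alpha .05, 80% power and a difference of 0.48 in HbA1c change.

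Teams and correlated outcomes are not mentioned in the last two sections. The article does not state how teams are formed, how large they are or how many participants use them.

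**The concern.** Participants are randomized one by one, but the intervention then links some of them on purpose. The Theoretical Basis section names teams and messaging among the sources of reinforcement and continued engagement. The team reward is tied to a primary outcome, and two 3-month reward periods are complete by the 6-month endpoint. If these features work as intended, members of a team will tend to change together. Controls have no such grouping up to 6 months, so the design is partially nested: clustered in one arm, independent in the other.

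A regression with the stated terms and a conventional variance treats every participant as independent. With positive within-team correlation, the intervention mean is less precise than that model reports. Confidence intervals are then too narrow and the 5% error rate is not held. This matters because the Study Design Overview frames the hypotheses as statistical significance.

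**Working it through.** **Step 1. Reproduce the planned sample size under independence.** Inputs from the Sample Size section: SD 1.4, difference 0.48, alpha .05 (taken as two-sided), power 80%.

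n per arm = 2 × (1.960 + 0.842)² × 1.4² / 0.48² = 133.5, rounded up to 134. The total is 268 and the power 80.1%. The stated 268 is reproduced with no design effect, so it contains no margin for team correlation.

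**Step 2. Variance with clustering in one arm.** Randomized numbers: 164 intervention, 176 control (Abstract, Results). Assumed, because the article does not give them: team size m, ICC, and share s of the intervention arm in teams.

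- Design effect in teams: DEFF = 1 + (m − 1) × ICC
- Weight of the intervention arm in the variance of the difference: (1/164) / (1/164 + 1/176) = 176/340 = 0.518
- Variance ratio, true to model: V = 1 + 0.518 × s × (DEFF − 1)
- SE ratio = √V
- Real two-sided alpha = 2 × [1 − Φ(1.96/√V)]

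| m | ICC | s | DEFF | V | SE ratio | Real alpha |
|---|---|---|---|---|---|---|
| any | 0 | any | 1.00 | 1.00 | 1.00 | 5.0% |
| 5 | 0.02 | 1 | 1.08 | 1.04 | 1.02 | 5.5% |
| 10 | 0.02 | 1 | 1.18 | 1.09 | 1.05 | 6.1% |
| 10 | 0.05 | 1 | 1.45 | 1.23 | 1.11 | 7.8% |
| 15 | 0.05 | 1 | 1.70 | 1.36 | 1.17 | 9.3% |
| 10 | 0.05 | 0.5 | 1.45 | 1.12 | 1.06 | 6.4% |

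Worked example, m = 15, ICC 0.05, s = 1: DEFF = 1 + 14 × 0.05 = 1.70; V = 1 + 0.518 × 0.70 = 1.36; √V = 1.17; 1.96/1.167 = 1.68; alpha = 9.3%.

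**Step 3. Read the ratio the right way round.** V = 1.36 means that the true variance is 36% larger than the model's. Equivalently, the model understates the true variance by 1 − 1/1.36, about 27%. At V = 1.04 both figures are about 4%.

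**Step 4. Check by simulation.** An unadjusted pooled two-sample test of 164 against 176, with everyone in the intervention arm in a team, was run 20,000 times per setting. It rejected in 4.9% of runs at ICC 0, 5.5% at m = 5 and ICC 0.02, and 7.4% at m = 10 and ICC 0.05. Over a wider grid (m 5 to 20, ICC 0.01 to 0.10) the formula gives 5.2% to 16.4% and the simulation 5.1% to 16.2%. The two agree closely.

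**Step 5. Effect on planned power.** With 134 per arm, the intervention arm carries half the variance and everyone is assumed to be in a team of 10. At ICC 0.02, V = 1 + 0.5 × 0.18 = 1.09, power for 0.48 falls from 80% to 77%, and 80% power needs 268 × 1.09, about 293 completers. At ICC 0.05, V = 1 + 0.5 × 0.45 = 1.225, power is 72%, and about 329 completers are needed.

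**The case against.** The best defence is that the quoted sentence names a model family and no variance estimator. It does not say that errors are independent, and a regression with cluster-robust standard errors is still a linear regression. This is a condensed article, and an analysis plan that is not shown could add a team effect. That is a fair limit on the point. It does not dispose of it: the article goes beyond naming a model family, gives the terms of the model, and adopts a sample size that reproduces only under full independence. Followed as written, the plan ignores a correlation that the intervention is designed to encourage.

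A reader might infer more than the article supports:

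- *That all intervention participants are placed in teams.* The team aspects are called optional and uptake is not given. Full membership is the upper bound for a given team size and ICC.
- *That the standard errors are too small as a matter of fact.* This depends on the ICC, team size and uptake. The effect is nil at ICC 0. With half the arm in teams of 5 and ICC 0.01, the SE ratio is only 1.005.
- *That teams are rewarded for their HbA1c level.* The reward is for average reduction.
- *That the variance is understated by up to 36%.* That figure is how much larger the true variance is. The understatement is at most about 27% in the assumed range.

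Two practical objections to a remedy also stand. Teams of 15 would give only about 164/15 = 11 clusters, too few for uncorrected robust standard errors. And the Data Analysis section promises analysis on masked data, whereas a team identifier present in one arm only would reveal allocation. Both are dealt with in the fix.

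**Conclusion.** The point holds in conditional form. The stated linear and logistic regressions and the sample size make no allowance for within-team correlation in the intervention arm. If that correlation is positive, the standard errors for HbA1c, glucose and weight are too small and the tests reject too often. The direction is clear, but the size cannot be fixed from the article.

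With the whole arm in teams of 5 to 15 and ICC 0.02 to 0.05, all assumed, the SE ratio is 1.02 to 1.17 and a nominal 5% test runs at about 5.5% to 9.3%. Half uptake brings the middle case (teams of 10, ICC 0.05) from 7.8% down to 6.4%. The effect therefore ranges from negligible to material. It does not show that the trial's result is wrong. It calls for an inexpensive improvement to the analysis.

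**What to change.** Keep the regression of change on treatment group and baseline value, and account for teams in one of two ways:

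1. team-clustered standard errors with a small-sample correction, each control and each intervention participant without a team being their own cluster; or
2. a partially nested mixed model with a random team effect in the intervention arm only, arm-specific residual variances, and controls and participants without a team as singletons.

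Apply the same to the logistic models. Report team size, uptake and the estimated ICC for each primary outcome, so that readers can see whether the adjustment mattered.

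**Cost.** Little new data should be needed, because the system has to link team membership to HbA1c change in order to rank teams. Confidence intervals will be somewhat wider: by up to about 17% under the assumptions above, and hardly at all if the ICC is near zero. To respect masking, fix the model in writing beforehand and release coded team identifiers only for the final run.

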**Blood pressure, mmHg, mean (SD)**					
	Systolic	130.4 (14.7)	130.4 (14.5)	130.4 (15.0)	.99
	Diastolic	82.3 (8.4)	82.6 (8.6)	82.0 (8.1)	.45
Weight, lbs, mean (SD)		204.8 (34.8)	205.6 (36.5)	203.9 (32.9)	.64
BMI, kg/m^2^, mean (SD)		31.1 (4.3)	31.2 (4.3)	31.1 (4.4)	.86
Waist circumference, cm, mean (SD)		102.8 (10.8)	103.1 (11.2)	102.5 (10.4)	.59
Glucose, mg/dL, mean (SD)		109.9 (8.4)	109.0 (8.3)	110.2 (8.6)	.52
HbA1c, %, mean (SD)		5.6 (0.3)	5.6 (0.3)	5.6 (0.3)	.94
Total cholesterol, mg/dL, mean (SD)		191.5 (31.7)	191.9 (33.0)	191.2 (30.2)	.83
LDL cholesterol, mg/dL^c^, mean (SD)		116.0 (27.6)	116.5 (27.9)	115.5 (27.3)	.72
HDL cholesterol, mg/dL^c^, mean (SD)		47.3 (14.0)	46.5 (13.0)	47.8 (14.5)	.40
Triglycerides, mg/dL^c^, mean (SD)		144.6 (73.7)	148.2 (68.8)	139.4 (67.3)	.24

^a^Significance of difference between intervention and control.

^b^Native American/Alaskan, Native Hawaiian/Pacific Islander, reported as multiple races or “other”. Ethnicity from EHR.

^c^For LDL: Control, n=172, Intervention, n=161; for HDL: Control, n=176, Intervention, n=162; for triglycerides: Control, n=174, Intervention, n=162; for waist circumference: Control, n=175, Intervention, n=163.

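### The randomisation is stratified on sex, BMI and race/ethnicity, but the primary model commits only to the baseline value, so the reported standard error may be too large for the design

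*Protocol article*

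**What the plan says.** Randomization and Blinding describes "blocked stratified randomization to achieve balance on sex, BMI (above/below 35), and race/ethnicity (white non-Hispanic, other"). That is 2 × 2 × 2 = 8 strata. The same section says that the demographic and BMI values used for allocation come from the online baseline questionnaire.

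Data Analysis specifies linear regression of change, in which "treatment group will be included as the primary predictor variable (intervention vs delayed control"), and then: "The baseline value of the outcome measure of interest will be included as a covariate". The next sentence keeps the model open: "Normality, interaction, and potential confounding will also be investigated, and potential confounders will be included as appropriate". The three stratification factors are not mentioned. The logistic models for binary outcomes are to follow a similar approach, so they share the gap.

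Measures and Data Collection gives the endpoints that the model serves: "The primary outcome of Alive-PD is change in HbA1c and fasting glucose at 6 months from baseline".

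**The concern.** When allocation is balanced within strata, the difference between arms no longer carries chance imbalance in the stratification factors. A model without those factors still counts the variance they explain as residual error. Its standard error then describes a less well-balanced design than the one used. If the factors are prognostic, confidence intervals are wider than they need be, the test runs below its nominal level and some power is given away.

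The rule for adding covariates does not repair this. Confounding in a trial shows itself mainly as imbalance between arms, and stratification is there to prevent imbalance in these factors. Table 1 shows no sign of it: P = .75 for sex, .86 for BMI (as a continuous measure) and .38 for race/ethnicity. A screen of that kind would tend to leave out the covariates that the design calls for, while others could enter by data-led choice. At stake are the reported intervals and power for HbA1c, fasting glucose and weight.

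**Working it through.** **Inputs from Sample Size.** "With an SD of 1.4 and an alpha of .05", a difference of 0.48, 80% power and 268 completers. The test is taken as two-sided.

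**Reproducing the plan's figure.** n per arm = 2 × (1.96 + 0.8416)² × 1.4² / 0.48² = 133.5, so 134 per arm and 268 in total. Power at 134 per arm is 80.1%. The stated 268 is reproduced; a one-sided test would give 212. This calculation uses the plain SD without covariates, so the present point does not make it wrong.

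**Input not in the documents.** R² is the share of variance in change, after the baseline value, that the strata explain. It is an assumption, taken from 0 to 0.10. The SD of 1.4 is treated as the SD before the strata are added.

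**Formulas.** Let k = √(1 − R²) and θ = 0.48 / (1.4 × √(2/134)) = 2.806. With idealised within-stratum balance:

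- Reported SE divided by true SE, strata omitted: 1/k.
- Type I error, strata omitted: 2 × [1 − Φ(1.96/k)].
- Power, strata omitted: Φ((θ − 1.96)/k). Power, strata included: Φ(θ/k − 1.96).
- Extra participants that the omitted model needs to match the included model: equating the two powers gives θ′ = θ + 1.96(1 − k), so extra N = 268 × [(θ′/θ)² − 1].

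| R² (assumed) | SE too large by | Type I error, omitted | Power omitted | Power included | Loss (points) | Extra N |
|---|---|---|---|---|---|---|
| 0 | 0% | 0.050 | 80.1% | 80.1% | 0 | 0 |
| 0.02 | 1.0% | 0.048 | 80.4% | 80.9% | 0.5 | 4 |
| 0.05 | 2.6% | 0.044 | 80.7% | 82.1% | 1.4 | 10 |
| 0.10 | 5.4% | 0.039 | 81.4% | 84.1% | 2.7 | 20 |

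Example for R² = 0.10: k = 0.9487, θ′ = 2.806 + 1.96 × 0.0513 = 2.907, and 268 × [(2.907/2.806)² − 1] ≈ 20. With all 340 randomised in place of 268, the same formula gives about 11 at R² = 0.05 and 22 at 0.10. The SE and type I columns do not depend on the SD of 1.4; the power and participant columns do.

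**Simulation check.** 268 participants, 8 strata, assumed blocks of 4, assumed stratum prevalences and 6,000 runs per setting. At R² = 0.10 the omitted model reported a mean SE of 0.171, while its estimate had an empirical SD of 0.1644. Type I error was 0.044 (Monte Carlo error about √(0.05 × 0.95/6000) = 0.003). Power was 80.7% omitted and 83.5% included. The included model's estimate had an empirical SD of 0.1639, so the estimate varies about equally under both models. The two models agreed at R² = 0.

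**The case against.** Four objections deserve an answer.

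**The model is not closed.** A reader might infer that the analysis adjusts for the baseline value alone. The text does not support that: the next sentence admits potential confounders, and nothing bars the strata. What stands is that baseline is the only covariate committed to in advance.

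**Covariate lists belong in a statistical analysis plan.** A journal article may leave the final list to the full plan, and silence would be no finding. But Data Analysis is not silent. It names one covariate and gives a rule for the others, and that rule suits a stratified trial poorly.

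**The size is easily overstated.** A reader might infer that the estimate itself is less precise and compute N/(1 − R²) − N, which at 340 gives 18 and 38 participants for R² of 0.05 and 0.10. That holds only if the estimate without the strata truly has the larger variance. Stratified allocation has already removed that variance; only the reported standard error misses it, so 11 and 22 are the right figures at 340. The type I errors in the table also assume perfect balance within strata, and the 164/176 split need not meet that. R² may be near zero, and for weight the baseline value already shares information with sex and BMI stratum. All of this stands, and it makes the point a small one.

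**The EHR race field.** A reader might infer that the model would use the field behind "Ethnicity from EHR", which is not reported for 42 of 340. That is a footnote to a descriptive table; no text says the field would enter an outcome model. It is a reason to name the source of the strata, not evidence of an error.

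**Conclusion.** The point holds as a modest improvement to the stated method. The design restricts allocation on three factors, the model commits to none of them, and the covariate rule would tend to pass them over. If they predict change beyond the baseline value, the reported standard error is too large, the intervals are too wide and the test is conservative. Over the assumed range of R² from 0 to 0.10 the cost at the planned sample is at most 2.7 power points, and nothing at R² = 0. It rests on that assumed R², on the plan's own 0.48 and 1.4, and on near-balance within strata.

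The documents support neither bias in the treatment effect nor an inflated type I error. The error runs in the conservative direction.

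**What to change.** In Data Analysis, name sex, BMI stratum (cut at 35) and race/ethnicity stratum (white non-Hispanic or other) as fixed covariates, together with treatment group and the baseline value, in the primary linear models and in the logistic models. Say that the values are those recorded by the randomisation system from the online questionnaire. Label adjustment for any other covariate as a sensitivity analysis.

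The cost is one sentence; the variables are already collected. There are two small downsides. Preliminary Outcome Results shows that treatment effects have already been examined, so the change must be dated and justified as an amendment. In the logistic models the treatment odds ratio becomes conditional on the strata, and the report should say so.
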